**Figure 2 F0002:**
[figure not shown]
Sampling procedure of primary healthcare facilities with 640 clinicians, Guangdong Province, China, January 2026 – December 2026

In the second stage, all primary healthcare institutions under the jurisdiction of the recruited local health authorities in these three cities will be included in the sampling frame. These institutions will then be regrouped into PSUs based on the number of clinicians. This ensures that each unit has a sufficient number of clinicians, preventing the exclusion of smaller institutions from the sampling process. The PSUs will then be sampled using a probability proportional to size (PPS) sampling method.

The study will be conducted as a cluster-randomized trial. The intervention will be delivered to the entire cluster (PSU), but the intervention’s effect will be measured at the clinician level. The measurement is based on the average performance of a random sample of clinicians within the cluster. This is achieved through unannounced standardized patient (USP) visits, which function as the final step of the sampling process. A minimum of 80 USP visits will be assigned to each experimental condition.

*Sample size and power*

Power analyses were conducted to determine the sample size needed to test the effect of the implementation strategies on our primary outcome, ‘clinician advice to quit’. The detailed definition and measurement of this outcome are provided in the section on study outcomes. Based on prior research, the baseline rate for this outcome was 33.9%^13^. Through stakeholder consultation, it was determined that a 40% increase in delivery, resulting in a final primary outcome of 47.46%, would be considered a clinically meaningful effect. Assuming a two-tailed test with an alpha level of 0.05 and a desired power of 0.8, a sample size of 28 participants per cluster is required. Accounting for the cluster-randomized design with a design effect (Deff) of 2 and adjusting for an anticipated 20% loss to follow-up, the sample size has been intentionally increased to further enhance statistical power for detecting higher-order interactions. Consequently, the required sample size for one experimental condition is approximately 80 participants. Given our study design with eight conditions (one condition per PSU, for a total of eight PSUs), this translates to 640 participants in total.

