		Daily cigarette consumption		Number of cigarettes smoked daily. To assess a reduction in smoking behavior.	Quantitative data and qualitative data	-	Telephone callback			●	●	●
	Tertiary outcome	Patient satisfaction with the BISC provided by the clinician		The patient’s perceived satisfaction with how the physician implemented BISC during the consultation.	Quantitative data and qualitative data	-	Telephone callback			●	●	

a I: Enrolment. II: Baseline (i.e. before the first of BISC implementation). III: Mid-term (i.e. at the middle of BISC implementation), which will be executed the weeks 1, 3, 5, 7, 9 and 11 after the start of the BISC implementation. IV: Endline (i.e. at the end of BISC implementation). V: Follow-up (i.e. maintenance of the BISC), which will be executed 6 months after the endline.

b Data collection via telephone callbacks with patients in periods I and V; Data collection by USP visits in period IV. IOF: Implementation Outcomes Framework. BISC: brief intervention for smoking cessation. USP: unannounced standardized patient.

*Outcomes*

The study outcomes will be aligned with the principles of Proctor’s Implementation Outcomes Framework (IOF) and the RE-AIM framework. According to the type 3 hybrid design, the outcomes are categorized into primary and secondary aims to reflect the dual focus on implementation strategies and patient-level effects.

Primary aim: implementation outcomes

The primary aim of this study is to evaluate the effectiveness of the implementation strategies. These outcomes will be assessed by a combination of methods to ensure a comprehensive evaluation.

The primary outcomes, ‘clinician ask smoking status’ and ‘clinician advise to quit’, will be assessed using unannounced standardized patient (USP) visits. These outcomes serve as key measures of fidelity to the brief intervention protocol. The secondary outcomes, ‘clinician ask about number of cigarettes smoked’, ‘clinician discuss the harms and benefits of quitting’, and ‘clinician provide a referral’, will also be measured using a combination of USP visits for clinicians and telephone callbacks for outpatients.

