### Data analysis

*Quantitative analysis*

Data will undergo de-identification prior to analysis. Baseline characteristics of participants will be presented, utilizing mean and standard deviation for continuous variables and frequency and percentage for categorical variables. The trial outcome analysis will adhere to the intent-to-treat principle. Generalized estimating equations (GEE) with a binomial distribution and log link function will be used for the primary binary outcome, with clustering specified at the PSU level, to assess the main and interaction effects of the four implementation techniques on adherence to BISC practices among primary healthcare clinicians. The model will account for robust predictors of outcomes, including baseline adherence scores and sociodemographic factors of clinicians^24-26^. Effect coding will be applied to each experimental condition, and subgroup analyses based on age, gender, clinician level, and facility will be conducted to further explore the impact of different technique combinations on BISC implementation. Sensitivity analyses, involving imputation of missing values through random forest, will be performed to validate the robustness of the findings^27^. For continuous outcomes, GEE models with a Gaussian distribution and identity link function will be employed, adjusting for the same covariates and clustering at the PSU level. In the analysis, control for covariates including clinician-related information (gender, age, professional title, and department) and patient-related information (gender, age, primary diagnosis, and smoking status). We will perform subgroup analyses on patient smoking status, level of tobacco dependence, and clinician department to investigate differences in BISC implementation among different types of clinicians for various types of patients.

Hypothesis tests will be two-sided, with statistical significance set at p<0.05. All statistical analyses will be performed using Stata version 16.0 and R version 4.5.2.

*Qualitative analysis*

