Qualitative data analysis from stakeholders will be de-identified and imported into Nvivo 11.0 for transcription, organization, coding, and content analysis. Our qualitative data analysis will use a mixed approach, combining both deductive and inductive methods, to identify established themes, patterns, and new discoveries^28,29^. For the first phase of the study, data from our scoping review^30^ and stakeholder consultations were analyzed deductively using the Consolidated Framework for Implementation Research (CFIR)^31^ to identify barriers and facilitators. For the second phase, data from semi-structured interviews will be analyzed inductively to find new themes. These data will also be analyzed using NPT to evaluate how the BISC intervention is integrated and sustained in practice. To ensure our coding is reliable, two team members will independently code each interview, and any differences will be resolved through discussion.

The systematic decision-making process^32^, guided by data from the factorial trial, will be integral to this procedure. We will leverage the estimated main effects to identify techniques that have a statistically significant positive impact. We will also examine interaction effects to glean insights into potential synergies or antagonisms between the techniques. The final optimization of implementation strategies will be achieved by integrating information from both main and interaction effects, along with a consideration of the predetermined constraints of the optimization objective. This approach ensures that the final selection of techniques is the most effective and efficient combination.

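### The trial is sized on one primary outcome but declares two, and the rule for selecting techniques does not say which one it uses

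*Protocol article*

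**What the plan says.** Four parts of the protocol article bear on the point.

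- **Sample size and power** uses one named outcome. The calculation was done "on our primary outcome, ‘clinician advice to quit", with a baseline of 33.9% and a target of 47.46% that stakeholders judged meaningful.
- **Outcomes (primary aim) and Table 2** declare two: "The primary outcomes, ‘clinician ask smoking status’ and ‘clinician advise to quit’, will be assessed using unannounced standardized patient (USP) visits". Table 2 places asking at the first step of the brief intervention and advising at the fourth, and scores each as 0 or 1.
- **Quantitative analysis** returns to the singular. The GEE model "will be used for the primary binary outcome, with clustering specified at the PSU level", and the outcome is not named. The effects are described as being "on adherence to BISC practices among primary healthcare clinicians", a third wording tied to neither outcome. One general rule covers significance: "Hypothesis tests will be two-sided, with statistical significance set at p<0.05".
- **The decision process**, at the end of the Data analysis section, states: "We will leverage the estimated main effects to identify techniques that have a statistically significant positive impact". No outcome is named there. The same paragraph adds that interaction effects and predetermined constraints are also weighed.

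The article does not rank the two outcomes, say whether success is needed on one or on both, or give a baseline, target or power for asking.

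**The concern.** The product of this trial is a selected package of techniques, and main effects are the first input to that selection. Asking and advising are different steps of the intervention, so a technique can move one without the other. An educational component might raise routine questioning about smoking and leave advice unchanged. For that result the plan gives no answer. The choice of endpoint could then be made after the estimates are known.

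A technique could also be kept on asking alone, which is neither the outcome the trial was sized on nor one with a stated meaningful effect.

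**Working it through.** **Inputs from the protocol.** Rates 33.9% and 47.46%; two-sided alpha 0.05; power 0.80; design effect 2; 20% loss; 8 conditions of about 80, 640 in total. Each factor level pools four conditions, so a main effect compares 320 with 320.

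**The plan's own figure.** The target reproduces: 0.339 × 1.4 = 0.4746. The base size of 28 per cluster does not. For two proportions,

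n = [1.96·√(2p̄q̄) + 0.842·√(p₁q₁ + p₂q₂)]² / (p₂ − p₁)², with p̄ = 0.4068,

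= (1.3616 + 0.5791)² / 0.1356² ≈ 205 per factor level, or 410/8 = 51.25 per condition. The later steps are 28 × 2 / 0.8 = 70, raised by stated choice to about 80, and 80 × 8 = 640. The mismatch over 28 is a separate problem. It matters here only because the calculation, right or wrong, uses one outcome.

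**If either outcome sufficed.** The rule asks for a positive effect, so a two-sided 0.05 test of an inert technique leads to selection only through the upper tail, 0.025. Under independence:

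- one technique, one outcome: 2.5%; two outcomes: 1 − 0.975² = 4.9%
- three techniques, one outcome: 1 − 0.975³ = 7.3%; two outcomes: 1 − 0.975⁶ = 14.1%

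The two outcomes are steps of one consultation scored for the same clinician, so positive correlation is likely. It lowers the two-outcome figures. With perfectly correlated test statistics the per-technique figure returns to 2.5%.

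**If both were required.** Error does not inflate, but power falls. The effective size per level is 320 × 0.8 / 2 = 128.

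- Nominal power for one main effect on advice: Φ[(√128 × 0.1356 − 1.3616)/0.6881] = Φ(0.25) = 59.9%.
- Both significant, assuming the same rates for asking: from 0.599² = 35.9% (independent) to 59.9% (fully correlated).

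**If alpha were split (0.025 each).** Power for advice falls to 48.7%, and the base size rises from 205 to 249 per level.

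**Power for asking.** The document gives no baseline, so these are assumptions. With the same relative 40% increase, two-sided 0.05 and 128 effective per level, power is 32% at a 20% baseline, 52% at 30%, 73% at 40% and 91% at 50%.

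All these powers take the protocol's design effect of 2 at face value. With one sampling unit per condition, eight in total, they are nominal only.

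**The case against.** The strongest reply is that much of this may be settled elsewhere. The article condenses a fuller protocol, and a statistical analysis plan could hold a multiplicity rule and a rule for two primary outcomes. Optimization trials may also choose not to control the familywise error rate. Two primary outcomes are legitimate when the success rule is stated. Selection does not rest on significance alone, because interactions and constraints also enter. This stands against any claim that the error rate is wrong or that multiplicity control is missing.

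A reader might go further and infer that each outcome is tested at 0.05, that either one admits a technique, and that false selection therefore rises from 5% to 9.75% per technique and from 14.3% to 26.5% over three. The document does not support that. It states no either-outcome rule, and the 0.05 level comes from a general sentence, not from a rule for each outcome. Those percentages also count significant effects in either direction, while the decision process asks for positive ones, so as selection rates they are about twice too high even under independence.

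What the reply does not remove is the conflict inside the article. It gives the number of primary outcomes in two ways and leaves the outcome behind the selection rule unnamed. Weighing interactions and constraints does not say which outcome the main effects refer to.

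**Conclusion.** The point holds as an inconsistency with a consequence for selection. The trial is sized, and its model is described, for one primary outcome; two are declared; and the endpoint for choosing techniques is not fixed. The outcome for a technique that moves asking but not advising is undefined, and asking has no stated planning basis.

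The size depends on a rule the document does not give. Under an either-outcome rule, the chance of a significant positive effect for an inert technique goes from 2.5% to at most 4.9%, and over three from 7.3% to 14.1%, assuming independence. Under a both-outcomes rule, nominal power for one main effect lies between 35.9% and 59.9%, assuming the same rates for asking and the protocol's own design effect and loss. The document does not establish that false selection is inflated, only that it leaves open which of these situations applies.

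**What to change.** Reconcile Sample size and power, Table 2, the Outcomes section, Quantitative analysis and the decision process before allocation is unblinded.

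- **Preferred:** name advising to quit, measured by unannounced standardized patient at endline, as the single primary outcome and as the outcome used for component selection. The sample size section already treats it that way. Make asking about smoking status the first secondary outcome. Alpha and N do not change on this account.
- **Alternative:** keep both as primary, state whether one or both must succeed, give the alpha for each, supply a baseline and target for asking, and restate power. With alpha split equally, the base size per level is 249 instead of 205. With design effect 2 and 20% loss that is 249 × 2 × 2 / 0.8 = 1,245 in total, against 205 × 2 × 2 / 0.8 = 1,025 for one outcome at 0.05.

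In either case, replace the reference to adherence in the model description with the named outcome or outcomes.

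The cost of the preferred change is mainly wording, but asking loses primary status. The stated study period began in January 2026, so a registry update or a dated amendment may be needed.

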### Study variables

*Demographic variables*

Demographic variables include institution information, clinician sociodemographics, and patient sociodemographics. Detailed variables, data collection methods, and time points are summarized in Table 2.

**Table 2 T0002:** Study variables of the type 3 hybrid effectiveness-implementation trial, Guangdong, China, January 2026 – December 2026

*Category*	*Outcome* *type*	*Variable*	*Theoretical basis*	*Definition*	*Variable type*	*Tool*	*Acquisition* *methods*	*Study periods ^a^*				
								*I*	*II*	*III*	*IV*	*V*
**Basic information**	Institution information	Institution location, level, etc.		-	-	-	Questionnaire survey	●				
	Socio-demographic of clinician	Gender, age, title, department, etc.		-	-	-	Questionnaire survey	●				
	Socio-demographic of patient	Gender, age, primary diagnosis, etc.					Telephone callback		●	●	●	●
**Implementation outcomes**	Primary outcome	Clinician asks smoking status	IOF: Fidelity RE-AIM: Implementation	From the first step in the BISC implementation steps in the China Clinical Cessation Guidelines (2015 edition), indicating whether the clinician asked smoking status or not.	Quantitative data, dichotomous variable (0,1)	Questionnaire	USP visit/telephone callback^b^		●	●	●	●
		Clinician advises to quit	IOF: Fidelity RE-AIM: Implementation	From the fourth step in the BISC implementation steps in the China Clinical Cessation Guidelines (2015 edition), indicating whether the clinician advised to quit.	Quantitative data, dichotomous variable (0,1)	Questionnaire	USP visit/telephone callback^b^		●	●	●	●
	Secondary outcome	Clinician asks about number of cigarettes smoked	IOF: Fidelity RE-AIM: Implementation	From the second step in the BISC implementation steps in the China Clinical Cessation Guidelines (2015 edition), indicating whether the clinician asked about number of cigarettes smoked.	Quantitative data, dichotomous variable (0,1)	Questionnaire	USP visit/telephone callback		●	●	●	●
		Clinician discusses the harms and benefits of quitting	IOF: Fidelity RE-AIM: Implementation	From the third step in the BISC implementation steps in the China Clinical Cessation Guidelines (2015 edition), indicating whether the clinician told about harms/benefits of quitting.	Quantitative data, dichotomous variable (0,1)	Questionnaire	USP visit/telephone callback^b^		●	●	●	●

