The secondary aim of this study is to assess the effects of the BISC intervention on patient-level outcomes. These outcomes will be measured via a patient phone call survey at two distinct time points. At the end of the intervention, a phone call will be made to all patients who were identified as smokers and received the BISC intervention during the study period. This initial survey will assess their smoking status immediately following the intervention and confirm their receipt of the BISC components. A 6-month follow-up survey will then be conducted exclusively with patients who self-reported as smokers and received the BISC intervention. This survey will assess the long-term effectiveness of the intervention by measuring key indicators, including 7-day point abstinence status, daily cigarette consumption, and patient satisfaction with the BISC provided by the clinician. A summary of all outcome measures, their respective assessment methods, and time points is presented in Table 2.

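### The endline source of three secondary fidelity outcomes is stated inconsistently, and the available endline patient calls reach only smokers who received BISC

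*Protocol article*

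**What the plan says.** All references are to the protocol article.

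- **Outcomes, primary aim.** The two primary items (asks smoking status, advises to quit) "will be assessed using unannounced standardized patient (USP) visits". The three secondary fidelity items "will also be measured using a combination of USP visits for clinicians and telephone callbacks for outpatients". No period is named for either statement.
- **Table 2.** The source column is the same for the primary and the secondary fidelity items: USP visit or telephone callback. Footnote b reads "Data collection via telephone callbacks with patients in periods I and V; Data collection by USP visits in period IV". It is attached to both primary items, to harms and benefits, and to referral. It is not attached to the row defined as "indicating whether the clinician asked about number of cigarettes smoked".
- **Outcomes, secondary aim.** The endline contact with patients is described thus: "a phone call will be made to all patients who were identified as smokers and received the BISC intervention during the study period". Besides smoking status, this call is to "confirm their receipt of the BISC components". The 6-month call is likewise limited to smokers who received BISC.

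**The concern.** At endline two kinds of record on the same BISC components will exist, and the article does not say clearly which one defines the secondary fidelity outcomes.

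The two records have different denominators. A USP visit is a scripted smoker consultation that counts whether or not the clinician acts. The endline call covers only consultations in which BISC took place. Because the items are themselves parts of BISC, the call sample is selected on something very close to the outcome. Its item rates describe what recipients were given, not how often smokers are given it.

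If an analyst took the word combination at face value and merged the records, the item rates and the estimated effect of each technique would depend on how many recipients were called in each condition. The secondary items would also no longer be comparable with the primary items, which are assessed by USP visits.

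**Working it through.** **1. The places side by side for period IV**

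| Item | Outcomes text | Table 2 with footnote b |
|---|---|---|
| Asks smoking status; advises to quit (primary) | USP visits | USP visits |
| Harms and benefits; referral | USP visits and callbacks | USP visits |
| Number of cigarettes | USP visits and callbacks | USP visit/callback, no footnote mark |

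The text separates primary from secondary items; the table does not.

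**2. Plan figures reproduced**

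- Sample size and power says "the baseline rate for this outcome was 33.9" percent, and 33.9% × 1.40 = 47.46%.
- 8 conditions × 80 USP visits = 640, and 20 USPs × 32 visits = 640.

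Both rates refer to advice to quit. The article gives no rate for any of the three secondary items, and no callback numbers.

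**3. Illustration of what merging would do**

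Inputs from the plan: 80 USP visits per condition; p = 33.9% with the technique absent and 1.4p = 47.46% with it present, borrowed from advice to quit.

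Assumptions: n recipients called in the technique-absent condition and 1.4n in the technique-present condition (proportional to delivery); the same item rate q among recipients in both.

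- Absent: (80p + nq) / (80 + n)
- Present: (80 × 1.4p + 1.4nq) / (80 + 1.4n)
- Ratio: 1.4 × (80 + n) / (80 + 1.4n)

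Both p and q cancel from the ratio. That follows from letting callbacks rise by the same factor of 1.40 as the USP rate, so it is not evidence of robustness. With q = 0.9:

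| n absent / present | Absent | Present | Ratio (USP only: 1.40) |
|---|---|---|---|
| 20 / 28 | (27.12 + 18) / 100 = 45.1% | (37.97 + 25.2) / 108 = 58.5% | 1.30 |
| 40 / 56 | (27.12 + 36) / 120 = 52.6% | (37.97 + 50.4) / 136 = 65.0% | 1.24 |
| 80 / 112 | (27.12 + 72) / 160 = 62.0% | (37.97 + 100.8) / 192 = 72.3% | 1.17 |

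If 80 recipients were called in each condition regardless of delivery, the rates would be 62.0% and (37.97 + 72) / 160 = 68.7%, a ratio of 1.11.

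**4. The direction is not fixed when q differs between conditions**

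Both examples use 80 and 112 callbacks and assumed item rates.

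- *Upward.* USP rates 5% and 7% (ratio 1.40), recipient rates 15% and 30%: (4 + 12) / 160 = 10.0% against (5.6 + 33.6) / 192 = 20.4%, a ratio of 2.04.
- *A false effect.* The item occurs in 10% of USP visits in both conditions (ratio 1.00) while BISC delivery is 33.9% and 47.46%. The recipient rates are then 10/33.9 = 29.5% and 10/47.46 = 21.1%. Each condition has 8 + 23.6 = 31.6 positives, so the rates are 31.6/160 = 19.8% and 31.6/192 = 16.5%, a ratio of 0.83.

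**The case against.** The strongest reply is that the article never pools the two sources. The Outcomes text names no period, footnote b divides the sources by period, and the article refers the reader to Table 2 for methods and time points. The limitations section also says that USP visits measure behaviour at a single time point. On this reading, combination means callbacks in some periods and USP visits at endline. The end-of-intervention call stands under the effectiveness aim and may serve only to confirm exposure. The missing footnote mark may be a typographical slip or a loss in text extraction.

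Much of this stands. A reader might infer that the plan merges the records and that the technique effects will therefore be biased toward no difference. The documents support neither step: pooling is not stated, and shrinkage needs similar recipient item rates in every condition.

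The period-based reading does not settle the matter, for three reasons. On that reading the primary items would be a combination too, since Table 2 gives them the same sources, yet the text sets them apart. Footnote b is not a clean key either: it assigns callbacks to period I, where these rows have no data point, and no source to periods II and III, where they do. Finally, Data analysis adjusts for patient gender and smoking status and plans subgroups by patient smoking status to examine BISC implementation. Both are constant across the USP cases, who are all male current smokers, so patient-reported records seem intended for some implementation models. That does not show pooling at endline, but it leaves it open.

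**Conclusion.** The inconsistency is real. For harms and benefits and for referral, the text and footnote b can be read as giving different endline sources; for number of cigarettes, nothing in the table excludes callbacks. It is also certain that the end-of-intervention call is restricted to BISC recipients, so its item rates cannot estimate fidelity among all smokers seen.

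The bias is conditional on the records being combined. In that case the rates would be inflated wherever recipient item rates exceed the USP rates, and the technique effects would be distorted. With equal recipient item rates and callbacks proportional to delivery, 1.40 falls to between 1.30 (20 callbacks in the technique-absent condition) and 1.17 (80 callbacks). These figures only illustrate, because they use advice-to-quit rates and assumed callback numbers. With unequal recipient rates the distortion can go either way.

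The primary outcomes are not affected. The article's rule for choosing techniques does not name these secondary items, so a wrong optimisation decision should not be inferred. This should be corrected before analysis, but it is a matter of secondary outcomes.

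**What to change.** 1. State that in period IV all five fidelity items, primary and secondary, come from USP visits only.
2. Attach footnote b to the number-of-cigarettes row of Table 2, and align the footnote's period labels with the periods marked in the table.
3. Reword the Outcomes sentence on the secondary items so that it agrees with the footnote and limits callbacks to the periods in which they are the intended source.
4. Report component receipt from the end-of-intervention call separately and descriptively, labelled as conditional on BISC receipt, and do not merge it with USP records.
5. Put the same label on any period V items taken from the 6-month call, which is also restricted to recipients.

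The cost is wording only, with no new data. The small downside is that the endline secondary items rest on the 80 USP visits per condition alone.
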